##### Secondary objectives

*Key secondary objectives*

The key secondary objectives are to determine the following anthropometric parameters in preterm infants born at ≤ 32 weeks of gestation at discharge and at 4 months:
Feeding toleranceVelocity of weight gainLength and head growthBody composition (by air displacement plethysmography, PeaPod)

*Other secondary objectives*
Neurodevelopmental outcome:
12 months corrected age: BSID-III (Bayley Scale of Development Third Edition)3.5 years of corrected age: BSID and WPSSI-IV (Wechsler Preschool and Primary Scale of Intelligence, Fourth Edition IV)Behavioural problems: parental assessment by CBCL (Child Behaviour Check List) at 3.5 years corrected ageTo compare the incidence of NEC, retinopathy of prematurity (ROP), and bronchopulmonary dysplasia (BPD) between both study groups

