#### Secondary outcomes

Growth (weight, length, head circumference) will be assessed at discharge and at 4 months of corrected age.Body composition (percentage of body fat, fat mass, fat-free mass) will be measured at discharge and at 4 months corrected age by air plethysmography (PeaPod).^1^Neurodevelopmental outcome:
12 months corrected age: BSID-III (Bayley Scale of Development Third Edition); the following stratification of index composite scores will be used in our study:< 70 (> 2 SD below the mean)—severe impairment70–84 (> 1 SD below the mean)—mild impairment≥ 85—normal development3.5 years of corrected age: BSID and WPSSI-IV (Wechsler Preschool and Primary Scale of Intelligence, Fourth Edition IV).Behavioural problems: parental assessment by CBCL (Child Behaviour Check List) at 3.5 years corrected age.Feeding tolerance under whole period of fortification.Morbidity: incidence of necrotizing enterocolitis (NEC), retinopathy of prematurity (ROP) and bronchopulmonary dysplasia (BPD), intraventricular haemorrhage (IVH), periventricular leukomalacia (PVL), sepsis, and pneumonia. Definitions provided below.

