### Sample size {14}

The sample size required to compare two means in two-sided equality test was estimated based on results from a prior double blind, randomized clinical trial, investigating the effect of TG vs SF of breast milk on the changes of anthropometric parameters and body composition in preterm children [23, 24]. It was determined that a mean difference of weight gain 1.9 g/kg/day between groups would be clinically important and feasible during intervention.

The following assumptions were made for the calculation: type I error (α) 5%, power 80%, equal sample sizes in both groups, the mean weight gain in the standard fortification group 19.3 g/kg/day, and the mean weight gain in the target fortification group 21.2 g/kg/day. To account for the higher uncertainty in measured weight gain due to differences between the studied and the quoted trial population, standard deviation value taken from the prior trial was increased by 50% to 3.75.

An estimated minimum size of each group is 68. Accounting for a presumed 20% attrition rate, due to potential dropouts, deviations from the protocol, and loss to follow-up, a minimum sample size required was estimated at 156 infants or 78 infants per treatment arm.

However, in order to detect a difference of 5 points in cognitive score of Bayley-III (secondary outcome) at 12 months of age (mean of 100 points, standard deviation (SD) 12) between the study groups with a power of 80% and α = 0.05, we have decided to increase the sample to 91 infants in each study group.

In summary, allowing for 10% of loss to follow-up, the target number of 200 premature infants will be recruited.

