### Statistical methods

#### Statistical methods for primary and secondary outcomes {20a}

Baseline characteristics will be presented for all included neonates in intention-to-treat and per-protocol analysis sets, by treatment group. Dichotomous variables will be presented as frequencies, categorical variables as median and interquartile ranges, and continuous variables as mean and standard deviations, along with 95% CI. In cases of missing data, i.e. due to adverse events or dropouts, in follow-up analysis, a weighted average taking account of changes in the gender ratio will be applied. Continuous variables will be tested against normality of distribution and the equality of variances between groups. For continuous variables distributed normally, the differences in means will be tested using *t* test; for continuous variables not distributed normally and for categorical variables between groups, comparison will be performed using the Mann-Whitney *U* test. The primary outcome will be assessed with one-tailed unpaired two-sample *t* test for noninferiority. Secondary and safety outcomes will be tested for two-sided superiority. Proportions of dichotomous variables will be tested using chi-square or Fisher’s exact test, whichever appropriate. In addition, the risk ratio (RR), the odds ratio (OR), and the number needed to treat will be assessed. For secondary outcomes, the difference will be considered significant when *p* value calculated in statistical tests will be < 0.05 or when the 95% CI for the mean difference will not include 0, or 1 in case of RR or OR.

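### At least 24 secondary outcomes are each declared significant at an unadjusted two-sided 0.05, and the one that set the sample size has no protected status

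*Protocol article*

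**What the plan says.** All references are to the protocol article.

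- **Decision rule.** Statistical methods for primary and secondary outcomes {20a} says "Secondary and safety outcomes will be tested for two-sided superiority". It then sets the criterion outcome by outcome: "For secondary outcomes, the difference will be considered significant when" the p "value calculated in statistical tests will be < 0.05 or when the 95% CI for the mean difference will not include 0" (or 1, for a risk or odds ratio).
- **Outcomes it applies to.** The Secondary outcomes list under Outcomes {12} includes "Growth (weight, length, head circumference) will be assessed at discharge and at 4 months of corrected age" and "Body composition (percentage of body fat, fat mass, fat-free mass) will be measured at discharge and at 4 months corrected age". It adds "12 months corrected age: BSID-III (Bayley Scale of Development Third Edition"), two instruments and a behaviour checklist at 3.5 years, feeding tolerance, and seven morbidities.
- **Tiers.** The Secondary objectives section has an upper tier: "The key secondary objectives are to determine the following anthropometric parameters in preterm infants". It covers feeding tolerance, growth and body composition. Neurodevelopment, including the 12-month Bayley-III, is in the lower tier of other secondary objectives. Neither Outcomes {12} nor Statistical methods {20a} refers to these tiers.
- **Sample size.** Sample size {14} powers one secondary outcome, the Bayley-III cognitive score at 12 months (difference 5, SD 12, power 80%, alpha 0.05), and on that basis says "we have decided to increase the sample to 91 infants in each study group".

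**The concern.** This is a stated decision rule, not a detail left to an analysis plan. A later plan could add a hierarchy only by overriding the published criterion. Applied to two dozen outcomes, the rule makes a chance finding likely, and nothing in the text says which finding would count as confirmatory.

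There is also a mismatch particular to this trial. The 12-month Bayley-III cognitive score raised the requirement from 78 to 91 infants per arm, yet it ranks below feeding tolerance among the objectives and is judged by the same rule as every other p value. A significant Bayley result would be one of many nominal results, although it is the only one that the trial was sized to test.

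**Working it through.** **1. The plan's own figure.** For two means, n per arm = 2 × (1.960 + 0.842)² × (SD/difference)². With SD 12 and difference 5, this is 2 × 7.849 × 5.76 = 90.4, rounded up to 91. The stated figure is reproduced by the normal approximation, and it spends the full two-sided 0.05 on this one outcome.

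**2. Count of tests from Outcomes {12}.**

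| Group | Tests |
|---|---|
| Growth: 3 measures × 2 times | 6 |
| Body composition: 3 measures × 2 times | 6 |
| Bayley-III at 12 months | 1 |
| BSID, WPSSI-IV and CBCL at 3.5 years | 3 |
| Feeding tolerance | 1 |
| Morbidities (NEC, ROP, BPD, IVH, PVL, sepsis, pneumonia) | 7 |
| **Total** | **24** |

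Without the morbidities the count is 24 − 7 = 17. The count allows one test per instrument, so it is a minimum. Further Bayley index scores or the impairment categories would add to it. The key tier alone holds about 13 (feeding tolerance, 6 growth, 6 body composition).

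**3. Chance of at least one significant result if there is no effect, independent tests.** Either direction: 1 − 0.95^k. Benefit only: 1 − 0.975^k, because a two-sided 0.05 test leaves 0.025 on the favourable side.

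| k | Either direction | Benefit |
|---|---|---|
| 24 | 1 − 0.95²⁴ = 70.8% | 1 − 0.975²⁴ = 45.5% |
| 17 | 1 − 0.95¹⁷ = 58% | 1 − 0.975¹⁷ = 35% |
| 13 | 1 − 0.95¹³ = 49% | 1 − 0.975¹³ = 28% |

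**4. Correlated tests.** The document gives no correlations, so these are assumptions. They were applied to 24 simulated normal test statistics with a common correlation, 200,000 replicates.

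| Correlation | Either direction | Benefit |
|---|---|---|
| 0.3 | about 60% | about 31% |
| 0.5 | about 46% | about 23% |
| 0.7 | about 31% | about 16% |

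A second model set correlation within domains only. It tested the eight binary outcomes by chi-square or Fisher's exact test at 91 per arm, with assumed event rates of 3% to 30%. Depending on the within-domain correlation, it gave 53% to 69% in either direction and 30% to 44% for benefit.

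**5. What a blanket correction would cost.** Bonferroni over 24 tests uses 0.05/24 = 0.00208 per test. At that level the Bayley-III comparison has 39% power with 91 per arm and would need 177 per arm for 80%. That is why the fix below names one outcome instead.

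**The case against.** Unadjusted testing of secondary outcomes beside one designated primary objective is common, and the protocol never claims a 5% familywise rate for them. Its 0.05 is a per-test criterion. That is fair: the figures above show what the rule implies, not a breach of a stated error rate. It does not remove the point, because the text calls each such result significant without marking it as nominal.

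The tests are not independent. Percentage fat, fat mass and fat-free mass are linked to one another and to weight, each is measured twice, and exact tests on rare morbidities run below their nominal level. This stands, and it is why the independence figures need the correlated ones beside them.

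Three stronger readings are tempting and should be set aside:

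- **That 71% is the chance of a false benefit.** It counts either direction. For benefit the figure is 45.5% under independence and lower with correlation. Body composition has no stated favourable direction, so some either-direction results could be presented as benefit, but that does not make 71% the right number.
- **That one secondary result could support a first-line recommendation even if the primary fails.** The Discussion in the Abstract makes this conditional on improvement in both growth and neonatal outcome, and growth is the primary domain.
- **That the Bayley-III result could not be told apart from chance findings.** Sample size {14} prespecifies its domain, age, difference, SD and power, which it does for no other secondary outcome. A careful reader can pick it out. What it lacks is confirmatory status in the objectives and the testing rule.

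**Conclusion.** The point holds. If targeted fortification has no effect, the stated rule gives a 71% chance of at least one significant secondary result in either direction under independence, and about 46% at a common correlation of 0.5. The corresponding chances of at least one apparent benefit are 45.5% and about 23%, against 2.5% for a single test. Leaving out the morbidities, for which adjustment is not advised, the independence figures are 58% and 35%.

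These results rest on the count of 24 (or 17), which is a floor, and on assumed correlations. The primary analysis is untouched. This is an inexpensive improvement to the reliability of secondary claims, not a flaw that threatens the trial.

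**What to change.** In Statistical methods {20a}, replace the blanket rule as follows:

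- Name the 12-month Bayley-III cognitive score as the single confirmatory secondary outcome, tested at two-sided 0.05. This keeps the 91 per arm of Sample size {14}.
- Report every other secondary outcome with its estimate and 95% confidence interval, labelled exploratory. Any p value is nominal, and no result is declared significant.
- Report morbidity and safety outcomes with confidence intervals and without multiplicity adjustment, so that no harm signal is suppressed.

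In Secondary objectives, move the 12-month Bayley-III to the key tier to match.

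Testing Bayley-III only after a significant primary result is optional. It cannot be run until the primary test is reconciled: Statistical methods {20a} describes a one-tailed noninferiority test, Trial design {8} a superiority trial, and Sample size {14} a two-sided test.

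**Cost.** No extra infants or data. The other secondary outcomes can no longer be claimed as confirmatory. Recruitment began in June 2019 according to Trial status, and the amendments section {25} requires a formal amendment with ethics approval for changes such as those to study objectives where they may affect conduct. Changing the tiers may therefore need one.

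### The either-or significance rule for secondary outcomes joins two different tests when Mann-Whitney is used, so its false-positive rate is somewhat above the stated 5%

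*Protocol article*

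**What the plan says.** Everything at issue is in the protocol article, section Statistical methods for primary and secondary outcomes {20a}, apart from the sample size.

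- A preliminary check comes first: "Continuous variables will be tested against normality of distribution and the equality of variances between groups".
- If the variable passes: "For continuous variables distributed normally, the differences in means will be tested using" the t test.
- If it does not: "for continuous variables not distributed normally and for categorical variables between groups, comparison will be performed using the Mann-Whitney" U test.
- Dichotomous outcomes: "Proportions of dichotomous variables will be tested using chi-square or Fisher"'s exact test, with RR and OR also reported.
- Direction: "Secondary and safety outcomes will be tested for two-sided superiority".
- Decision rule for secondary outcomes: significant when the p value is below 0.05 "or when the 95% CI for the mean difference will not include 0, or 1 in case of RR or OR".

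The section Sample size {14} sets the level for the Bayley-III cognitive score, a secondary outcome: "with a power of 80% and α = 0.05, we have decided to increase the sample to 91 infants in each study group".

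**The concern.** A confidence interval for a mean difference belongs to a test of means. Mann-Whitney compares ranks. When an outcome fails the normality check, the p value comes from one method and the interval from the other, and the two can fall on opposite sides of the threshold. The rule does not say which governs in that case. It accepts whichever is favourable.

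A rule that rejects when either of two non-equivalent 5% tests rejects must reject more often than each test alone. At stake is the interpretation of borderline results among the continuous secondary outcomes: growth measures, body composition, developmental scores and behavioural scores. A result called significant at 0.05 may have been reached by a looser rule. This is a stated decision rule, not a detail left to an analysis plan.

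**Working it through.** **Reproducing the plan's own figure.** Inputs from Sample size {14}: difference 5 points, SD 12, two-sided α 0.05, power 80%.

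n per arm = 2 × (1.960 + 0.842)² × 12² / 5² = 2 × 7.849 × 5.76 = 90.4, rounded up to 91.

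This matches the stated 91 (power at 91: 80.3%). The level of 0.05 and n = 91 are the reference values below.

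**Rate of the either-or rule when there is no difference.** Both arms were drawn from the same distribution, 91 per arm, 40,000 repetitions. The protocol names no normality test, so a 5% omnibus test on the residuals was assumed. A pass leads to the t test and a failure to Mann-Whitney. The outcome counts as significant if that p is below 0.05 or the t-based 95% CI excludes 0. The Monte Carlo standard error is √(0.07 × 0.93 / 40,000) = 0.0013, or 0.13 points.

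| Assumed distribution | Chosen test only | Either-or rule |
|---|---|---|
| Normal | 5.00% | 5.05% |
| Uniform | 5.05% | 5.35% |
| Skew-normal | 5.02% | 6.28% |
| t, 5 df | 5.09% | 6.33% |
| Gamma, shape 4 (skewness 1.0) | 4.98% | 6.41% |
| Gamma, shape 2 | 4.94% | 6.83% |
| Lognormal, log-SD 0.5 | 4.92% | 6.91% |
| t, 3 df | 5.15% | 6.94% |
| Exponential | 5.08% | 7.14% |
| Normal with 10% contamination | 4.99% | 7.22% |
| Lognormal, log-SD 1 | 4.84% | 7.42% |
| Lognormal, log-SD 1.5 | 5.08% | 7.48% |

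With 78 or 100 per arm the picture is the same. The highest value is 7.8% (lognormal, log-SD 1, 100 per arm).

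**Shapes nearer to the listed outcomes.** With Shapiro-Wilk in each arm as the normality check, 91 per arm and 20,000 repetitions, the either-or rule gave:

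- normal scores with mean 100 and SD 12, rounded to 5-point steps: 5.8%
- gamma with skewness 0.4 or 0.5: 5.6% and 5.7%
- lognormal with log-SD 0.15 or 0.25: 5.5% and 6.4%
- t with 10 df: 6.0%
- gamma with skewness 1.0: 6.3%
- exactly normal data: 5.6%, against 5.3% for the t test alone in the same run

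**How often the two criteria disagree.** Disagreement = 2 × (rate of either) − (rate of t) − (rate of Mann-Whitney).

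- Gamma, shape 4: 2 × 0.0641 − 0.0494 − 0.0498 = 0.029
- Exponential: 2 × 0.0714 − 0.0486 − 0.0508 = 0.043
- Lognormal, log-SD 1: 2 × 0.0742 − 0.0449 − 0.0484 = 0.055

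So the two criteria give opposite answers in about 3 to 6% of null comparisons of these kinds.

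**Dichotomous outcomes.** Exact enumeration at 91 per arm gave, for a rule combining chi-square/Fisher with Wald intervals for RR and OR, 2.8% at 5% incidence, 5.1% at 10%, 4.9% at 20%, 5.0% at 30% and 5.1% at 40%. At 100 per arm the maximum was 5.2%. There is no material inflation.

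**The case against.** The strongest reply is that the word or merely restates one 5% criterion in two forms, and that the phrase about a mean difference fits only the t-tested outcomes, where p value and interval agree. The section does speak of differences in means only for normally distributed variables, and the authors may have meant no more than this. But the rule is written for secondary outcomes without restriction, and equivalence fails once Mann-Whitney supplies the p value. Even on the kind reading, the text does not say what governs when the two disagree.

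The second reply is about size, and it largely stands. A reader might infer that the true level for secondary outcomes is 7 to 8%. The documents do not support that as a general statement. They give no distribution for non-normal outcomes, and the Bayley-III score is described only by mean 100 and SD 12. Rates of 7% and above need strong skew or heavy tails, which are hard to imagine for head circumference or a Bayley score, though a behavioural checklist score could be more skewed. For milder shapes the excess over 5% is about 0.5 to 1.4 points.

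The third reply also stands: the consequence is limited, because the rule cannot affect the primary outcome or, in practice, the dichotomous morbidity outcomes.

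**Conclusion.** The point holds in a limited form. For secondary outcomes analysed by Mann-Whitney, the rule as written is a union of two different tests and exceeds its nominal two-sided 5%. The rate is about 5.5 to 6.5% for near-normal to moderately skewed outcomes, just under 7% for somewhat stronger skew (gamma with shape 2, lognormal with log-SD 0.5), and up to about 7 to 8% under strong skew or heavy tails. For light tails (uniform) it stays near 5.3%. With one criterion per outcome the rate is 4.8 to 5.2% for every shape in the table.

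These figures assume 91 per arm, a t-based interval for the mean difference, an unnamed normality check filled in by a common one, and distributions that the protocol does not state. The direction does not depend on those choices, but the size does. Outcomes that are truly normal are affected only through occasional misclassification by the normality check. It would also be wrong to infer that Mann-Whitney must be abandoned: the fault lies in joining the two criteria, not in either test.

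**What to change.** In Statistical methods for primary and secondary outcomes {20a}, replace the either-or condition with one governing criterion per outcome, fixed before unblinding, and take the interval from the same method as the p value:

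- t-tested outcomes: the t test p value with its 95% CI for the mean difference.
- Mann-Whitney outcomes: the Mann-Whitney p value with a Hodges-Lehmann interval.
- Dichotomous outcomes: the chi-square or Fisher p value decides, and RR and OR with their CIs are reported as estimates.

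Using the t-based analysis for all continuous outcomes would also remove the problem. It is an option on which statisticians differ, not a requirement.

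The cost is one sentence, with no extra data or patients. The downside is that a few borderline secondary results will no longer be called significant. In the gamma shape 4 case, for example, that is 6.41% − 4.98% = 1.43 points, or about 14 in 1,000 null comparisons.

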#### Interim analyses {21b}

Due to the short duration of recruitment and low risk of potentially serious outcomes, an interim analysis will not be performed.

#### Methods for additional analyses (e.g. subgroup analyses) {20b}

Given the homogeneity of our study groups, we do not plan to conduct any subgroup analyses.

#### Methods in analysis to handle protocol non-adherence and any statistical methods to handle missing data {20c}

Linear regression will be used to fill missing data.

In addition, a sensitivity analysis using (1) missing as missing (i.e. no imputation) for dropouts and (2) last observation carried forward (LOCF method) will be performed for the primary endpoint to explore the impact of missing data after a subject drops out. All participants will be included in the intention-to-treat (ITT) analysis, regardless of adherence. In addition, per-protocol (PP) analysis of patients with complete observations will be performed to estimate the effect of missingness or protocol deviations on the statistical analysis.

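### Missing primary data are filled by linear regression and then analysed by an ordinary t test, so the standard error is too small or the treatment effect is diluted, depending on an imputation model the plan does not state

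*Protocol article*

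**What the plan says.** All references are to the protocol article.

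- The missing-data section {20c} gives one unqualified rule: "Linear regression will be used to fill missing data". It then lists, for the primary endpoint, "a sensitivity analysis using (1) missing as missing (i.e. no imputation) for dropouts and (2) last observation carried forward (LOCF method) will be performed". The regression fill is therefore the main method, and no imputation and LOCF are secondary to it. A per-protocol analysis of infants with complete observations is also planned.
- The same section says: "All participants will be included in the intention-to-treat (ITT) analysis, regardless of adherence".
- Statistical methods {20a} states: "The primary outcome will be assessed with one-tailed unpaired two-sample *t* test for noninferiority". No multiple imputation, residual draw or variance adjustment is attached to this test.
- Section {20a} also says that, for missing data, "in follow-up analysis, a weighted average taking account of changes in the gender ratio will be applied".
- Sample size {14} uses 1.9 g/kg/day, an SD of 3.75 and a two-sided 5% level. The primary calculation begins "Accounting for a presumed 20% attrition rate", and that rate covers protocol deviations as well as dropout and loss to follow-up. The final target of 200 infants, which is driven by the Bayley score, allows 10% loss.
- Outcomes {12} has weights taken daily up to 4 weeks and weekly after that until discharge.

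**The concern.** A regression prediction lies on the fitted line and has no residual scatter. An ordinary t test on a mixture of observed and predicted values goes wrong in one of two ways, depending on a choice that section {20c} leaves open.

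- **Arm is among the predictors.** The estimate is unbiased under random missingness. However, the sample variance is too low and the sample size too high, so the confidence interval is too narrow and a true null is rejected too often.
- **Arm is not among the predictors.** Infants with filled values receive the same expected outcome in both arms, so the estimated difference shrinks towards zero.

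Either way the primary confidence interval does not have its stated coverage. Sections {20c} and {20a} also give different fill rules whose scopes overlap for follow-up outcomes. Weighting by sex ratio does not deal with dropout related to illness or growth.

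**Working it through.** **Inputs from the article.** Planned difference 1.9 and SD 3.75 g/kg/day, so 1.9/3.75 = 0.507 SD. The target of 200 gives n = 100 per arm (91/0.9 = 101). Missing fraction f is taken as 0.10 or 0.20, the two attrition figures in Sample size {14}. The article has no figure for error rates under imputation, so there is none to reproduce.

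**Assumptions.** Data are missing completely at random, equally in both arms. One deterministic fill is made from a predictor unrelated to arm. Its R-squared is not given in the article, so a range is shown. No level is stated for the one-tailed primary test; 5% is assumed and both versions are given.

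**Arm in the model, by formula.**

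- SE the t test reports: SD × √[(2/n)(1 − f(1 − R²))]
- True SE of the estimate: SD × √[(2/n)(1 − fR²)/(1 − f)]
- Ratio r = √[(1 − f)(1 − f(1 − R²))/(1 − fR²)]
- Type I error: 2Φ(−1.96r) two-sided, Φ(−1.645r) one-sided

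Example, f = 0.20 and R² = 0.3, in SD units: reported SE √(0.02 × 0.86) = 0.131; true SE √(0.02 × 0.94/0.80) = 0.153; r = 0.856. Type I error is 9.4% two-sided and 8.0% one-sided. The ratio does not contain n, so the sample size is immaterial to this result.

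A simulation with 100 per arm (20,000 runs per row, Monte Carlo standard error about 0.2 points) gives:

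| Missing | R² | r (formula) | Two-sided: formula / simulated | One-sided: formula / simulated | Simulated 95% CI coverage |
|---|---|---|---|---|---|
| 10% | 0.1 | 0.910 | 7.5% / 7.8% | 6.7% / 7.1% | 92% |
| 10% | 0.3 | 0.929 | 6.9% / 7.0% | 6.3% / 6.5% | 93% |
| 10% | 0.5 | 0.949 | 6.3% / 6.4% | 5.9% / 6.3% | 94% |
| 10% | 0.85 | 0.984 | 5.4% / 5.3% | 5.3% / 5.2% | 95% |
| 20% | 0.1 | 0.818 | 10.9% / 10.8% | 8.9% / 8.9% | 89% |
| 20% | 0.3 | 0.856 | 9.4% / 9.4% | 8.0% / 8.0% | 91% |
| 20% | 0.5 | 0.894 | 8.0% / 8.0% | 7.1% / 7.2% | 92% |
| 20% | 0.85 | 0.967 | 5.8% / 5.9% | 5.6% / 5.5% | 94% |

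The limit at R² = 0 is r = 1 − f, which gives 7.8% and 11.7% two-sided.

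**Arm left out.** The expected estimate is (1 − f) × 1.9: 0.9 × 1.9 = 1.71 and 0.8 × 1.9 = 1.52 g/kg/day. Simulation agrees (0.46 and 0.41 SD). At the planned effect, 95% CI coverage is about 93% to 94% with 10% missing and 88% to 89% with 20% missing (R² 0.1 to 0.85, 8,000 runs each). The two-sided zero-difference test at R² = 0.3 rejects 5.1% and 4.8% of the time.

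**Alternatives in the same setting.** Multiple imputation with Rubin's rules (R² = 0.3, 20 imputations, 2,000 runs) gives two-sided type I error of 4.0% (10% missing) and 5.2% (20% missing), with coverage of 96% and 95%. Its CI width is 0.580 and 0.609 SD, against 0.537 and 0.516 SD for the single fill with arm in the model. The single-fill interval is thus 7% narrower (0.537/0.580 = 0.93) or 15% narrower (0.516/0.609 = 0.85). Complete-case analysis holds about 5%.

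**The case against.** **The article does not say that the fill is single or deterministic.** It is a condensed account, and imputation details often sit in an analysis plan that is not shown. This is fair as far as it goes: that filled values count as observed is a reading of a plain regression fill followed by a plain t test. But section {20c} does name a main method and attaches nothing that would correct the variance, so this is a stated choice and not a blank. Even one random residual draw per missing value would leave the t test too liberal.

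**Missing primary data may be well below 20%.** This stands. The 20% includes protocol deviations, and infants who deviate or stop the intervention stay in follow-up and in the intention-to-treat set. The annual loss rate of at most 20% in the retention section {18b} concerns longer follow-up. The 10% column is at least as plausible.

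**Strong predictors would nearly remove the problem.** This also stands. If the regression used an infant's own earlier weights and R-squared were about 0.85, the error would be close to nominal. The article does not say that it will.

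**The planned no-imputation analysis is a safeguard.** It is valid when data are missing completely at random, and a discrepancy with the main result could reveal the problem. It does not correct the main result.

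**Stronger readings a reader might infer.** One is that the article gives two contradictory rules for the primary outcome. The sex-ratio rule is limited to follow-up analysis, whereas the primary outcome is in-hospital growth, so the overlap is shown only for follow-up outcomes. Another is that LOCF assumes the infant stops growing. That follows only if weight is carried forward; carrying forward a velocity does not imply it, and LOCF is only a sensitivity analysis here.

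**Conclusion.** The concern holds in conditional form. Followed as written, the main analysis counts regression-filled values as data, and its confidence interval is wrong under either version of the imputation model.

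- **Arm included, R-squared 0.1 to 0.5:** type I error is about 7% two-sided (6% to 7% one-sided) with 10% missing, and about 8% to 11% two-sided (7% to 9% one-sided) with 20% missing. The two-sided figure approaches 12% if the predictors explain nothing and is near nominal at R-squared of about 0.85.
- **Arm omitted:** there is no inflation of the zero-difference test, but 1.9 g/kg/day shrinks to about 1.7 or 1.5.

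A reader might infer that the false-positive rate is inflated and the effect diluted together. The text does not support that: these are alternative faults under alternative models. Nor does it support an unconditional claim of about 11%, which needs arm in the model, 20% truly missing, weak predictors and a two-sided test. The fault is modest at 10% missing and material at 20%. These sizes rest on missingness completely at random and on assumed R-squared values.

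**What to change.** In section {20c}, replace the regression fill as the main method by one of:

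- multiple imputation done separately by arm, with baseline variables (such as site, delivery mode, gestational age and birth weight) and earlier weights as predictors, combined by Rubin's rules; or
- a likelihood-based mixed model on the serial weights already collected.

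Keep the no-imputation analysis as a sensitivity analysis. In section {20a}, drop the sex-ratio weighted average for follow-up outcomes, or state its scope and reconcile it with {20c}, whose rule has no such limit. Settle the wording before unblinding.

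The cost is a change of text and slightly more analysis work, with no new data or recruitment. Confidence intervals become wider than under the current plan: at R-squared 0.3, by about 8% with 10% missing (0.580/0.537 = 1.08) and 18% with 20% missing (0.609/0.516 = 1.18). That width reflects the information actually available.
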